#### Primary outcome

The primary outcome of interest will be the Problematic Pornography Consumption Scale (PPCS) (Bőthe, Tóth-Király et al., 2018b). The PPCS assesses past-six-month PPU covering six factors: salience, tolerance, mood modification, withdrawal, relapse, and conflict (Griffiths, 2005). The scale includes 18 items with three items per each factor. Respondents indicate answers on seven-point scales (1 = “never”; 7 = “all the time”). Higher scores on the scale indicate higher levels of PPU. A score of 76 (out of 126) or higher indicates a high-risk of PPU.

#### Secondary outcomes

Besides the PPCS, the *frequency of pornography us*e (one question) (Bőthe, Bartók et al., 2018a; Bőthe, Tóth-Király et al., 2019b), *duration of pornography use* per each occasion (one question) (Bőthe, Bartók, et al., 2018a; Bőthe, Tóth-Király et al., 2020), *previous treatment-seeking* (two questions) (Bőthe, Tóth-Király et al., 2020), *perceived addiction* to pornography use (one question) (Grubbs et al., 2019), and *moral incongruence* regarding pornography use (one question) (Grubbs et al., 2019) will be assessed with pre-established questions.

Pornography craving will be measured with the one-factor *Pornography Craving Questionnaire (PCQ)* (Kraus & Rosenberg, 2014) including 12 items rated on a seven-point scale (1 = “disagree completely”; 7 = “agree completely”). Items assess current pornography craving. Higher scores on the scale indicate higher levels of craving for pornography use.

Self-efficacy regarding pornography use will be measured with the one-factor *Pornography-Use Avoidance Self-Efficacy Scale (PASS)* (Kraus, Rosenberg, Martino, Nich, & Potenza, 2017), including 18 items. Participants indicate their confidence in relation to avoiding pornography use (0% = “not confident at all”; 100% = “completely confident”). Higher scores on the scale indicate higher levels of craving for pornography use.

Participants' current level of *sexual satisfaction* (one item) (Mark, Herbenick, Fortenberry, Sanders, & Reece, 2014) will be assessed with one reliable and valid pre-established question.

Beliefs about the changeability of sexual life will be assessed with the one-factor *Sex Mindset Scale* (SMS) (Bőthe et al., 2017), including five items (three reverse coded items) rated on a six-point scale (1 = “strongly disagree”; 6 = “strongly agree”). Higher scores on the scale indicate higher levels of beliefs in the malleability of one's sexual life.

Participants' satisfaction with their life will be assessed with the one-factor *Satisfaction with Life Scale* (SWLS) (Diener, Emmons, Larsen, & Griffin, 1985), including five items rated on a seven-point scale (1 = “strongly disagree”; 7 = “strongly agree”). Higher scores on the scale indicate higher levels of satisfaction with one's life.

Participants' current levels of general positive and negative feelings will be assessed with the ten-item *Positive and Negative Affect Scale* (PANAS) (Gyollai et al., 2011). The scale includes two factors (positive affect and negative affect) with five items per each factor rated on a five-point scale (1 = “very slightly or not at all”; 5 = “extremely”). Higher scores on the factors indicate higher levels of positive and negative affect, respectively.

### Data analyses

Data will be analyzed on an intention-to-treat basis. Missing data will be handled by applying multiple imputations with 100 iterative estimations per value (Schafer & Graham, 2002). Demographic variables and other baseline variables will be inserted into the prediction model to estimate missing values. Differences in the outcomes between the treatment and control conditions will be examined with linear mixed models (LMM). LMMs will be specified appropriately to model clusters and repeated measures by defining random effects for study arms and time (repeated measures). For non-normal continuous outcomes, appropriate distributions (e.g., zero-inflated) will be specified. Additionally, per-protocol analyses will be conducted.

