### Sample size calculation

Two groups (treatment vs. control group) will be compared over time (t_0_, t_1_, t_2_, and t_3_). Based on the results of previous PPU reduction interventions (Crosby, 2011; Crosby & Twohig, 2016; Minarcik, 2016), small effect sizes (Cohen *d* = 0.2) may be anticipated when comparing the treatment and control conditions. After calculations conducted with the G*Power software, a sample size of 121 in each study group would have 80% power to detect the difference with an alpha error of 5% and two-tailed testing. Therefore, the recruitment of a minimum of 242 participants would be sufficient to detect differences between the treatment and control groups over time.

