### Randomization and trial flow

After the baseline assessment, randomization will take place at an individual level by an automated, computer-based algorithm on the intervention website. A randomization list will be created in a 1:1 ratio. After the randomization, participants in the intervention condition will receive immediate access to the online intervention, while participants in the control condition will receive access to the intervention three months after the completion of the baseline questionnaire. Participants will know to which group they have been assigned. The intervention condition will last six weeks. Follow-up assessments will be completed online and will take place right after the end of the six-week-long intervention (t_1_), at a one-month follow-up (t_2_), and three-month follow-up (t_3_) (Fig. 1). If the final assessment is not completed, up to two reminders will be sent out 2 and 5 days later.

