However, some limitations of the present study should be mentioned. First, dropout rates are expected to be high in line with reports from previous online intervention studies (Rooke, Copeland, Norberg, Hine, & McCambridge, 2013; Schaub et al., 2015). Second, online interventions are often characterized by a low adherence rate because of the distant nature of the interventions (e.g., lack of personal relationships or non-personalized exercises) (Amann et al., 2018). Third, individuals with PPU who are currently receiving psychosocial or pharmacological treatments to reduce their PPU will be excluded from the study. Fourth, individuals who are more familiar with the use of the Internet may be more likely to participate in the study that may result in self-selection bias (Wantland, Portillo, Holzemer, Slaughter, & McGhee, 2004). Fifth, all measures will be self-reported, which may result in report bias. However, anonymous, online, self-reported data collection may be beneficial in sexuality-related studies when participants are asked to report about sensitive topics and problematic behaviors by alleviating stress resulting in more honest responses (Griffiths, 2012).

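### The stated multiple-imputation predictors are all demographic or baseline variables; followed as written, study arm and the follow-up outcomes are left out and the treatment effect is attenuated by roughly the share missing

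*Protocol article*

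**What the plan says.** The Data analyses section sets the analysis population ("Data will be analyzed on an intention-to-treat basis"), the handling of missing values ("Missing data will be handled by applying multiple imputations with 100 iterative estimations per value") and then the predictors ("Demographic variables and other baseline variables will be inserted into the prediction model to estimate missing values"). The treatment comparison is by linear mixed models with repeated measures over t0 to t3.

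Study arm and the follow-up scores do not appear among the predictors. The Study design and Randomization and trial flow sections both place randomisation after the baseline questionnaire, so arm is not a baseline variable in the ordinary sense, and t1 to t3 scores cannot be.

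On how much will be missing, the Discussion says that "dropout rates are expected to be high in line with reports from previous online intervention studies". No rate is given anywhere.

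**The concern.** An imputation model should contain at least the variables whose relationship the analysis model estimates. Here the analysis estimates an arm difference over time, while the predictors named for imputation include neither arm nor the repeated outcome.

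Two consequences follow and should be kept apart.

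- **Arm omitted.** Participants with missing scores receive values from a distribution pooled over both arms. These records contribute no treatment difference beyond chance differences at baseline, and they dilute the difference among observed participants. The plan anticipates only a small effect and high dropout, so the risk is a false null result on the primary outcome.
- **Earlier follow-up scores omitted.** A participant's t1 and t2 scores are likely to be strong predictors of the later score and of dropping out. If dropout depends on them, missing-at-random does not hold given baseline variables alone. Imputed values also lose the within-person link to the observed follow-up scores, which the mixed model uses.

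**Working it through.** **Inputs.** From the article: d = 0.2 and 121 per arm (Sample size calculation), 1:1 allocation (Randomization and trial flow), assessments at t0 to t3. Assumed, because the article gives no figure: share missing, correlation between assessments, and dropout mechanism. The article has no figure for dropout or imputation to reproduce. Whether 121 per arm follows from d = 0.2 is a different question; the proportional shrinkage below does not depend on it.

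**Closed form, arm omitted.** Let the control mean be μ and the intervention mean μ − d. Let p1 and p0 be the shares missing in the intervention and control arms, with dropout unrelated to outcome. The pooled imputation model gives both arms an imputed mean of μ − w·d, where w is the intervention arm's share of the observed data: w = (1 − p1) / [(1 − p1) + (1 − p0)]. The completed-data difference is

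d × [(1 − p1) + (p1 − p0) × w].

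With p1 = p0 = p this reduces to d × (1 − p):

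- 30% missing: 0.2 × 0.7 = 0.14
- 50% missing: 0.2 × 0.5 = 0.10
- 70% missing: 0.2 × 0.3 = 0.06

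With unequal dropout, for example 60% and 20% (average 40%): w = 0.4 / 1.2 = 0.333, and 0.2 × (0.4 + 0.4 × 0.333) = 0.107. The equal-dropout formula at 40% gives 0.12, so strict proportionality needs similar dropout in both arms.

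**Simulation check.** 121 per arm, true effect 0.20 at each follow-up, correlation 0.6 between assessments, monotone dropout completely at random, Bayesian regression imputation (5 imputations), 600 replicates, baseline-adjusted arm difference at t3:

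| Missing at t3 | 0.2 × (1 − p) | Baseline only | Baseline + earlier scores, no arm | Baseline + arm | Baseline + arm + earlier scores |
|---|---|---|---|---|---|
| 20% | 0.16 | 0.164 | 0.173 | 0.205 | 0.195 |
| 30% | 0.14 | 0.139 | 0.158 | 0.208 | 0.204 |
| 40% | 0.12 | 0.117 | 0.147 | 0.203 | 0.195 |
| 50% | 0.10 | 0.091 | 0.132 | 0.201 | 0.197 |
| 60% | 0.08 | 0.080 | 0.118 | 0.214 | 0.194 |

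The standard deviation of the estimates across replicates ranged from 0.075 to 0.183, so the Monte Carlo error is about 0.003 to 0.007 (0.075/√600 to 0.183/√600). The 60%/20% case gave 0.105, against 0.107 from the formula.

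Three readings follow. Omitting arm attenuates as the formula says. Adding arm removes the attenuation, even without the earlier scores. Adding earlier scores without arm only softens it.

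**Dropout that depends on t1.** A second simulation used a true effect of 0.36, which is an assumption and not the article's value, with correlation 0.6, 10 imputations and a baseline-adjusted comparison at t2. Baseline-only imputation gave 0.251, 0.175 and 0.102 at 30, 50 and 70% missing. Divided by 0.36, these are 0.70, 0.49 and 0.28, again close to 1 − p. Including arm and t1 gave 0.371, 0.364 and 0.366.

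When dropout was related to t1 in opposite directions in the two arms, at 50% missing, imputation from arm and baseline gave 0.531, a bias away from zero. Adding t1 gave 0.357. Reversing which arm loses its high scorers would reverse the sign of that bias.

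**The case against.** The strongest reply is that the sentence never says the list is complete. A reader might infer that the plan excludes study arm; the article does not say so. The reference to iterative estimation even suggests a procedure in which incomplete variables predict one another, which would bring in the follow-up outcomes. This is also a condensed, preregistered article, and a full variable list commonly belongs in a statistical analysis plan. All of this stands as a limit on certainty: the attenuation is what results from following the sentence, not something the authors are shown to intend.

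It does not remove the point. The article is not silent and does not defer the matter; it chooses to name the predictors, and every class it names is demographic or baseline. Stretching the phrase about other baseline variables to cover arm would still not reach the t1 and t2 scores.

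A reader might also infer that both omissions pull the effect toward zero in exact proportion to dropout. That is too strong. Omitting earlier scores alone left the estimate at about 0.20 under random dropout and pushed it away from zero in the arm-opposed case. Proportionality itself is approximate and needs similar dropout by arm.

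Finally, the simulations use a single-visit baseline-adjusted comparison, not the planned mixed model, and the correlation and dropout mechanisms are assumed. The closed form for the arm omission depends on neither the correlation nor the imputation software.

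**Conclusion.** The point holds in conditional form. As written, the imputation sentence leads to a model without study arm or follow-up outcomes. Under that model, with similar dropout in both arms, the anticipated d = 0.2 would be estimated at about 0.14, 0.10 or 0.06 at 30, 50 or 70% missing. The direction is certain if arm is omitted and dropout is unrelated to outcome. The size depends on a dropout rate that the article does not state beyond expecting it to be high.

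The missing t1 and t2 scores are a second, distinct defect. They cause no attenuation by themselves, but they weaken the missing-at-random assumption and allow bias of either sign when dropout depends on those scores differently in the two arms.

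**What to change.** Extend the sentence to say that the imputation model includes study arm (or is run separately by arm) and the outcome at all assessments t0 to t3, alongside the demographic and baseline variables already named.

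An equally acceptable route is to fit the planned linear mixed model by likelihood to all observed data as the primary analysis, and to keep the corrected imputation as a sensitivity analysis.

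Module completion and similar adherence data should not be a predictor common to both arms, because wait-list controls have no module data during the waiting period. They could be used only within the intervention arm, if imputation is run by arm.

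The cost is one sentence and slightly more programming. Arm is known for everyone, and Table 3 already schedules the PPCS at all four assessments.

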Currently, there is a gap in the literature with respect to evidence-based, scalable, online interventions that can effectively reduce PPU. Therefore, the aim of the present study is to test the effectiveness of a web-based self-help program (Hands-off) to reduce PPU in a two-armed randomized controlled trial (RCT), while also considering psychopathological comorbidities. The primary outcome will be the change in the level of PPU between baseline and follow-up assessments (after the end of the six-week-long intervention (t_1_), at a one-month follow-up (t_2_), and three-month follow-up (t_3_)) compared to a control condition. The secondary outcome measures will include beneficial changes in the intervention groups' pornography use frequency, pornography craving, pornography use-avoidance self-efficacy, beliefs about the malleability of sexual life, sexual satisfaction, negative and positive emotions, and life satisfaction over time compared to the control group.

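### The primary effect is defined as change from baseline with no baseline adjustment stated in the outcome model; stating one would gain precision at no cost

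*Protocol article*

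**What the plan says.** The Introduction states: "The primary outcome will be the change in the level of PPU between baseline and follow-up assessments", at t1, t2 and t3, against a control condition. The Hypotheses section uses the same baseline-versus-follow-up framing. The sample size section treats t0 as one level of time: "Two groups (treatment vs. control group) will be compared over time (t_0_, t_1_, t_2_, and t_3".

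Under Data analyses, the method is given as "Differences in the outcomes between the treatment and control conditions will be examined with linear mixed models (LMM". The only model terms named there come in the phrase "by defining random effects for study arms and time (repeated measures". No fixed effects are listed, baseline PPCS is not named as a covariate, and nothing is said about whether the arms share a baseline mean. The one stated use of baseline data is in imputation: "Demographic variables and other baseline variables will be inserted into the prediction model to estimate missing values".

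The order of events is clear: "After the baseline assessment, randomization will take place at an individual level". Every randomised participant should therefore have a baseline PPCS that treatment cannot have influenced.

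**The concern.** An effect defined as change, a time factor that includes t0, and a repeated-measures mixed model usually lead to arm, time and arm-by-time terms with baseline means estimated separately by arm. With complete data the arm-by-time contrast in that model is the between-arm difference in change scores. It ignores a known fact: randomisation follows the baseline assessment, so both arms have the same expected baseline mean.

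What is at stake is precision. The change score carries the full noise of the baseline measurement. It also over-corrects any chance difference between arms at baseline, because it subtracts the whole difference, not the part that predicts follow-up. The price is wider intervals and lower power for the primary comparison. The article expects high dropout and states no allowance for it in the sample size, so precision has real value here.

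**Working it through.** **Inputs from the article.** 121 per arm, d = 0.2, two-sided 5%, 80% power (Sample size calculation); 1:1 allocation (Randomization and trial flow); assessments at t0 to t3 (Table 3); PPCS covering the past six months (Primary outcome).

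**Assumptions.** The correlation ρ of PPCS between any two assessments is not given, so a range of 0.3 to 0.9 is used. The SD is equal at all assessments and set to 1, d is in units of that SD, and data are complete.

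**The plan's own figure.** For a two-sample comparison, n per arm = 2(1.960 + 0.842)²/0.2² = 393. With 121 per arm, SE = √(2/121) = 0.1286, 0.2/0.1286 = 1.556, and power = Φ(1.556 − 1.960) = 34.3%. The stated 80% is not reproduced. A repeated-measures interaction test with f = 0.1 and four measurements comes near 242 in total only at a correlation of about 0.12, which the article does not state. That is a separate point; here it only shows that the article supplies no ρ to work from.

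**Step 1: one follow-up.** Per-arm variance of the change score: 1 + 1 − 2ρ = 2(1 − ρ). Per-arm variance after baseline adjustment: 1 − ρ². The ratio is (1 − ρ)(1 + ρ)/[2(1 − ρ)] = (1 + ρ)/2, below 1 for every ρ below 1.

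Power uses SE = √(2v/121), where v is the per-arm variance. At ρ = 0.5, the change score has v = 1.00, SE = 0.1286 and power 34.3%. Adjusted, v = 0.75, SE = 0.1113, 0.2/0.1113 = 1.796, and power = Φ(1.796 − 1.960) = 43.5%.

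| ρ (assumed) | v, change | v, adjusted | reduction | power at 121 per arm | n per arm for 80% |
|---|---|---|---|---|---|
| 0.3 | 1.40 | 0.91 | 35% | 25.9% → 37.1% | 550 → 358 |
| 0.5 | 1.00 | 0.75 | 25% | 34.3% → 43.5% | 393 → 295 |
| 0.7 | 0.60 | 0.51 | 15% | 51.9% → 58.6% | 236 → 201 |
| 0.9 | 0.20 | 0.19 | 5% | 93.6% → 94.6% | 79 → 75 |

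**Step 2: mean of t1–t3, same effect at each.** Change: (1 + 2ρ)/3 + 1 − 2ρ. Adjusted: (1 + 2ρ)/3 − ρ². At ρ = 0.5 these are 0.667 and 0.417, a ratio of 0.625. The ratios at ρ = 0.3, 0.7 and 0.9 are 0.475, 0.775 and 0.925. Power moves from 36.3% to 64.7% (ρ = 0.3), 47.8% to 67.4% (0.5), 69.1% to 79.8% (0.7) and 98.9% to 99.3% (0.9).

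**Step 3: where the loss arises.** Mixed models with t0 in the response were fitted to 150 simulated trials at each of two correlations, with 121 per arm and the effect averaged over t1–t3. With free baseline means the average SE was 0.105 (ρ = 0.5) and 0.081 (ρ = 0.7). With t0 still in the response but one common baseline mean, it was 0.083 and 0.071, against theoretical baseline-adjusted values of 0.083 and 0.072. The free baseline means cause the loss, not the presence of t0.

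**Step 4: where ρ may lie.** If six months is about 26 weeks and t1 falls about 6 weeks after baseline, (26 − 6)/26 = 77% of the t1 recall window precedes randomisation. At t2, about 10 weeks after baseline, the share is (26 − 10)/26 = 62%. Overlap of this size may raise ρ and so shrink the gain, but this is inference.

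**The case against.** The strongest reply is that the criticised model is inferred. The article does not list fixed effects, does not say outright that t0 is in the response vector, and does not say that baseline means are free. An effect described as change can be estimated by a baseline-adjusted model, because with equal expected baselines the adjusted difference in follow-up level is also the difference in change. The analysis section is plainly condensed: the psychopathology measures listed as control variables do not appear in its model text either. Covariates are often left to an analysis plan, and neither that nor the preregistration is shown.

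Much of this stands. A reader might infer that the trial has decided against baseline adjustment; the article does not say that. A reader might also infer that including t0 as a repeated outcome itself wastes information; Step 3 shows that it does not. Nor do the documents support a claim of bias, since over repeated randomisations both analyses are unbiased. Finally, no single power gain can be quoted for this trial: ρ is unknown, dropout is expected, and the gain ranges from large to about 5% of the variance.

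The reply does not remove the point. The article does fix the effect as change from t0, does count t0 as a time level, and does say where baseline variables enter, without naming the outcome model. Followed as written, it leads most naturally to the less precise contrast.

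**Conclusion.** The point holds as one of efficiency. On the usual reading, the primary contrast is a difference in change scores and is less precise than one that uses the pre-randomisation PPCS, at any ρ below 1. For a single follow-up the avoidable variance is 35% to 5% as ρ runs from 0.3 to 0.9. For the mean of three follow-ups it is 52.5% to 7.5% (one minus the ratios 0.475 and 0.925). These figures rest on assumed correlations, equal variances, complete data and, for the mean, equal correlation between all assessments. If ρ is near 0.9, as the recall window might make it, the practical gain is small. The change is worth making, but its absence would not invalidate the trial.

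**What to change.** Under Data analyses, specify the primary mixed model with fixed effects for arm, time and arm-by-time, and choose one of two forms:

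- (a) model PPCS at t1–t3 with baseline PPCS and its interaction with time as covariates; or
- (b) keep t0 as an outcome and constrain the arm means to be equal at t0.

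Both estimate the same between-arm difference in change, so the definition of the primary outcome can stay.

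Treat each secondary outcome in the same way with its own baseline value, where schedule and distribution allow. Table 3 has PANAS only at t0 and t3, so a baseline-adjusted model of t3 serves there. For outcomes given a non-normal distribution, enter baseline as a covariate, without claiming the (1 + ρ)/2 gain.

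The cost is a sentence or two in the analysis section; no new data or assessments are needed. The choice should be recorded before outcome data are examined by arm.
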